**Figure 2 fig2:**
[figure not shown]
EduFAST web platform flowchart.

To ensure maximum adherence, platform usage metrics will be monitored on a weekly basis and data entry on a monthly basis.

### Data collection

2.5

The investigator team will collect data retrospectively from electronic prescription modules, NHs and microbiology unit records. During the pre-intervention phase, the data will be collected using a case report form (eCRF) in Microsoft Excel©. During the intervention phase, the data will be collected using the EduFAST web platform.

To evaluate the impact of the web platform as an ASP tool and assess the potential of using wastewater for surveillance, the following variables will be recorded monthly:*Variables related to the use of the web platform*: number of visits to the web platform, number of NHs registered, activity on the web platform (reports, completed training, etc.), and the average score on knowledge and satisfaction questionnaires.*Variables of antimicrobial use*: Defined Daily Dose (DDD) according to the World Health Organization (27), globally (Anatomical Therapeutic Chemical (ATC) groups J01 + J02), and for specific antimicrobials (amoxicillin, amoxicillin/clavulanic acid, cefixime, other cephalosporins, azithromycin, clarithromycin, ciprofloxacin, levofloxacin, moxifloxacin, clindamycin, metronidazole, sulfamethoxazole/trimethoprim, and fosfomycin trometamol). We will also record the number of prescriptions for the aforementioned antimicrobials, both individually and globally.*Clinical variables*: number of residents, number of hospital admissions, number of hospital admissions due to infections, and number of hospital admissions due to adverse effects of antimicrobials.*Microbiological variables*: number of isolations of MDR microorganisms (ESBL-producing *E. coli*, ESBL-producing *Klebsiella pneumoniae*, carbapenemase-producing *Enterobacteriaceae*, MRSA, MDR *P. aeruginosa*, and MDR *A. baumannii*) in clinical samples and also in nasal and rectal or perineal swab samples (only in selected NHs); and number of DNA or toxin detection for *C. difficile* in clinical samples.*Environmental variables (only in selected NHs)*: concentration of antimicrobials and their metabolites (amoxicillin, methylated amoxicillin, (5R,5S)-amoxicillin, clavulanic acid, cefixime, azithromycin, clarithromycin, levofloxacin, ciprofloxacin, moxifloxacin, clindamycin, clindamycin sulfoxide, metronidazole, hydroxy-metronidazole, sulfamethoxazole and trimethoprim), and concentration of MDR microorganisms (ESBL-producing *E. coli*, ESBL-producing *K. pneumoniae*, carbapenemase-producing *Enterobacteriaceae*, MRSA, MDR *P. aeruginosa*, MDR *A. baumannii*) in wastewater samples.

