### Intervention

2.2

The intervention consists of the implementation of antimicrobial stewardship strategies through the EduFAST web platform in participating NHs, to optimize antimicrobial use, improve infection management, and strengthen surveillance of antimicrobial resistance.

The intervention phase began at the end of 2025 and will continue throughout 2026. During this period, healthcare professionals from participating NHs will have access to the EduFAST platform and will be encouraged to use its different modules as part of routine clinical practice.

The intervention includes three main components:Educational component. Healthcare professionals will have access to training materials hosted on the platform, including treatment guidelines for the most common infectious syndromes in NHs, audiovisual materials, infographics, and simulated clinical cases. Participants will complete questionnaires assessing baseline knowledge, acquired knowledge, and satisfaction with the training activities.Monitoring of antimicrobial use and resistance indicators. Participating centers will enter monthly data on antimicrobial consumption, clinical outcomes, and microbiological indicators. The platform will automatically calculate predefined indicators, allowing centers to monitor antimicrobial use and resistance trends.Results reporting and feedback. The platform will generate periodic reports summarizing the indicators for each participating center. These reports will allow users to compare their center’s results with aggregated data from other participating NHs and will provide recommendations to improve antimicrobial prescribing practices and infection management.

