### EduFAST web platform: design and development

2.4

In terms of technological structure, the web platform will include a backend component, which will provide administration and data management features, and a web platform.

The web platform will consist of the following modules:*General project information module*. It will consist of two sections. The first will contain information about the research project, the web platform, and the research team. The second section will provide information about the participating NHs, with a map showing the location of each center. Access to this module will be public and available to all users.*Training module*. It will include treatment guidelines for the main infectious syndromes in NHs, audiovisual materials, infographics, and simulated clinical cases aimed at healthcare professionals from the participating centers. There will also be questionnaires on prior knowledge, questionnaires to assess acquired knowledge, and a satisfaction questionnaire. Access to this module will be restricted to participants, editors and administrators.*Data entry module*. Participants will be able to enter the numerators and denominators for each study indicator (antimicrobial use indicators, clinical indicators, and microbial resistance indicators). The web platform will then automatically calculate the final value of each indicator. Table 2 shows the indicators with their respective numerators and denominators. Access to this module will be restricted to participants, editors and administrators.*Results presentation and reporting module*. This module will consist of three sections. The first section, “Result Presentation,” will display the indicator results through tables and figures. This section will offer two levels of access: open access for web users, who will be able to view aggregated information on antimicrobial consumption across all participating NHs; and participant access, which will allow users to analyze their own data and compare their center’s results with the aggregated results of other centers with similar characteristics. The second section, “Result Reports,” will allow participants to download personalized reports containing their results, along with key recommendations or strategies to be implemented in the center based on deviations identified in relation to the average value of each indicator. Access to these modules will be restricted to participants, editors and administrators. The third section, “Result Maps,” will display the results of all indicators aggregated by autonomous communities on a map, and will be available only for editors and administrators.*Contact, help, and frequently asked questions (FAQs) module*. It will provide users with information on how to use the tool through materials that include both text and video instructions.*Private area*. This section will provide access to advanced features depending on the user’s role. Participants will be able to view registered users associated with their center, as well as review, modify, or delete related data. Editors/administrators will have access to features related to the maintenance, management, and generation of usage statistics for the web platform (logins, centers, users, generated reports, downloads, and interaction with materials).

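### Outcome recording moves from an Excel form to the platform as the intervention phase starts, so a step in recording cannot be separated from the level change; who collects in each phase also needs reconciling

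*Protocol article*

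**What the plan says.** On the tool, section 2.5 (Data collection) is explicit. Before the intervention: "During the pre-intervention phase, the data will be collected using a case report form (eCRF) in Microsoft Excel". Afterwards: "During the intervention phase, the data will be collected using the EduFAST web platform".

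On the collector, the sections do not agree plainly. Section 2.5 opens with "The investigator team will collect data retrospectively from electronic prescription modules, NHs and microbiology unit records", which names no phase. Section 2.2 (Intervention) makes data entry by the centers part of the intervention: "Participating centers will enter monthly data on antimicrobial consumption, clinical outcomes, and microbiological indicators". Section 2.4 repeats this for the data entry module: "Participants will be able to enter the numerators and denominators for each study indicator". The platform then computes each indicator.

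Section 2.9 (Statistical analysis) fits a segmented regression with a starting level, a starting slope, a step at the intervention and a change of slope. It adds an autoregressive term, seasonal adjustment where needed, and a mixed model with a random intercept per center. The Discussion confirms that there is no comparison group without the intervention.

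Three features bear on comparability between phases. Section 2.5 uses the WHO definition of DDD without distinguishing phases. Table 2 sets one denominator, the monthly resident count. Section 2.4 has data entry monitored monthly, to support adherence.

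**The concern.** An interrupted time series without a control attributes whatever happens at the interruption to the intervention. Here the recording route changes at that same point. If months on the platform are less complete, more complete, or counted differently from months on the Excel form, the difference enters the estimated step. Total antimicrobial consumption, the main variable, is exposed to this, as are prescriptions, admissions and isolates.

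The condensed format of an article does not explain the problem away. The switch is a stated feature of data collection, and no later choice of model can undo it without further data. The limitations in the Discussion mention uneven adherence to recording between homes, but not the change of recording between phases.

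**Working it through.** The plan gives no figure for agreement between the two recording routes, so there is none to reproduce. The check is whether the planned model can separate the two effects, and what happens if it cannot.

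**Inputs.** The four-parameter segmented model is from section 2.9. The switch of tool at the start of the intervention phase is from section 2.5. Series lengths are assumed: 12+12 months (borrowed from the wastewater schedule in section 2.6.2), and also 18+12 and 18+18. The size of a recording shift is assumed, because the document gives none.

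**Step 1: identifiability.** Let t be the month, T the first intervention month, and D = 1 if t ≥ T, otherwise 0. The model is

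Y = b0 + b1·t + b2·D + b3·D·(t − T) + error.

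Let R = 1 for months recorded on the platform and 0 for months on the Excel form. Under section 2.5, R = D in every month. Adding a term b4·R gives b2·D + b4·R = (b2 + b4)·D, so only the sum can be estimated. Numerically, the design matrix has rank 4 with 4 columns. With R added it stays at rank 4 with 5 columns, for all three series lengths. The autoregressive term and the random intercept do not help, because R switches within every center at the same point as D.

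**Step 2: size of the distortion.** Take a flat series at 1 with no true effect, and a recording shift s from T onwards. The fitted values are:

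| Assumed shift s | Level change | Trend change |
|---|---|---|
| −0.05 | −0.05 | 0 |
| −0.10 | −0.10 | 0 |
| +0.10 | +0.10 | 0 |

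The transfer is one for one by construction. The table shows where a shift would go, not that one exists. With a true step e, the observed step is (1 + e)(1 + s) − 1. For a true −20%, s = −0.10 gives 0.80 × 0.90 − 1 = −28%, and s = +0.10 gives 0.80 × 1.10 − 1 = −12%. The error can therefore inflate or hide an effect.

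**Step 3: a gradual change.** Suppose completeness falls linearly by 10% over the first 6 of 12 intervention months and then stays there. The fit gives a level change of −0.039 and a trend change of −0.0073 per month. The slope is not protected either.

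**Step 4: what restores separation.** A month recorded by both routes contributes two rows that differ only in R. Their difference is (0, 0, 0, 0, 1), so R is no longer a copy of D. With 3 doubly recorded months the matrix reaches rank 5 of 5.

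**The case against.** The strongest reply is that only the tool changes. The sentence about the investigator team is not limited to a phase, section 2.3 uses the word investigators for people working in nursing homes, and section 2.3.1 requires every center to be able to supply the data. The same people may therefore be working from the same records throughout. This stands to the extent that a change of collector is an inference. A reader might infer from sections 2.2 and 2.4 that collection passes from the investigator team to center staff, but the document does not establish that. What it does establish is that the sections need reconciling and that the tool changes.

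Second, one DDD standard and one denominator cover both phases, the sources are not said to change, and entry is monitored monthly. These points lower the risk, particularly for DDDs. Common definitions do not show that both routes apply them alike, however, and the monitoring is described as serving adherence, not accuracy against source.

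Third, a reader might infer that centers can alter outcome values on which they are benchmarked. The sentence reads "Participants will be able to view registered users associated with their center, as well as review, modify, or delete related data". It may refer to user or center records, and ordinary correction rights are no evidence of bias. The point does not rely on it.

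Fourth, wastewater concentrations are measured alike in both phases and do not depend on platform entry. That is correct, but only three homes take part, so they cannot stand in for the main variable.

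Finally, sections 2.1 and 2.2 date the start of the intervention differently (July 2025 and the end of 2025). If platform recording and the other components began at different times, the effects could be separated in part. No such staggering is planned.

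**Conclusion.** The concern holds as a problem of identifiability. The recording tool switches with the phase, the design has no control, and the planned model cannot distinguish a step in recording from the level change. The collinearity is exact for every series length tried. It rests only on the switch in section 2.5 and the model in section 2.9.

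The size and direction of any bias are unknown. The 5-10% range is an assumption used to show the transfer. Set beside the 20% effect in section 2.3.2 it would be a quarter to a half (5/20 and 10/20), but that section does not say that its 20% is a level change, so the comparison is only a rough guide. A reader might infer that the study will show a false fall in consumption. The documents do not support that: fuller capture on the platform would bias the other way, and the shared definitions may keep the shift small. The bias is possible and unchecked, not demonstrated. It should be addressed because it touches the main variable and can still be examined.

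**What to change.** 1. State in section 2.5 who collects and who enters the data in each phase, and reconcile this with sections 2.2 and 2.4.
2. Re-extract 2-3 intervention months per center from the source records by the baseline method. Alternatively, enter some baseline months through the platform route.
3. Report agreement between the two routes for total DDD, prescriptions and number of residents.
4. Add a sensitivity analysis of the level change corrected for any difference found.
5. If agreement is poor, use source-record extraction in both phases for the impact analysis and keep platform values for feedback to centers.
6. List the change of recording among the limitations.

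The cost is 2-3 months × about 10 centers, or about 20-30 center-months of extraction by a method that is already retrospective. No added participants are needed. With the intervention running through 2026 and results expected in early 2027, there is time to do it. Re-extracting the whole intervention phase would cost considerably more, about 12 months × 10 centers = 120 center-months, and is needed only if agreement proves poor.

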**Methods:**

Quasi-experimental, multicenter, before-and-after study. The intervention phase will last 12 months and involves implementing ASP strategies (educational measures, indicator monitoring and periodic feedback) via the EduFAST web platform. Information will be collected on the use of the web platform, user satisfaction, knowledge gained and the number of website visits. To assess the impact of EduFAST’s implementation, the following data will be recorded: clinical variables; antimicrobial consumption and prescription profiles; and the incidence of infections caused by multidrug-resistant bacteria and *Clostridioides difficile*. Additionally, the presence and concentration of antimicrobials, multidrug-resistant microorganisms and resistance genes in wastewater from the participating centers will be recorded to evaluate the correlation between clinical samples, antimicrobial consumption and wastewater findings, as well as the environmental impact of the intervention. The intervention’s impact will be analyzed through interrupted time series analysis, trend analysis, mixed linear regression models and correlation analysis for data obtained from wastewater samples.

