
**Table 2 tab2:** Indicators from the EduFAST study.

Indicator		Definition
Antimicrobial use indicators	Numerators	Monthly total Defined Daily Dose (DDD) of antimicrobials (ATC groups J01 + J02) Monthly DDD of specific antimicrobials (amoxicillin, amoxicillin/clavulanic acid, cefixime, other cephalosporins, azithromycin, clarithromycin, ciprofloxacin, levofloxacin, moxifloxacin, clindamycin, metronidazole, sulfamethoxazole/trimethoprim, fosfomycin trometamol, and other antimicrobials) Monthly number of total antimicrobial prescriptions (ATC groups J01 + J02) Monthly number of prescriptions of specific antimicrobials
	Denominator	Number of residents in the month
Clinical indicators	Numerators	Monthly number of hospital admissions Monthly number of hospital admissions due to infections Monthly number of hospital admissions due to adverse effects of antimicrobials
	Denominator	Number of residents in the month
Microbiological indicators	Numerators	Monthly number of extended-spectrum beta-lactamase-producing *Escherichia coli* isolates Monthly number of extended-spectrum beta-lactamase-producing *Klebsiella pneumoniae* isolates Monthly number of carbapenemase-producing *Enterobacteriaceae* isolates Monthly number of methicillin-resistant *Staphylococcus aureus* isolates Monthly number of multidrug-resistant *Pseudomonas aeruginosa* isolates Monthly number of multidrug-resistant *Acinetobacter baumannii* isolates Monthly detection of DNA or toxin for *Clostridioides difficile*
	Denominator	Number of residents in the month

The flowchart corresponding to the web platform menu, which can only be accessed by participating users is shown in Figure 2.

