In conclusion, implementing this project involves developing an interactive web platform to facilitate professional training and enable monitoring of indicators related to antimicrobial resistance and use in NHs. This initiative is expected to generate significant health benefits, including reducing overall antimicrobial consumption in these settings, optimizing prescribing patterns by further limiting the use of broad-spectrum antibiotics, reducing infections caused by MDR bacteria and *C. difficile*, and facilitating ASP interventions in NHs. Wastewater analysis will provide insight into the correlation between antimicrobial consumption, microbial resistance, and the environment, exploring its potential use for surveillance.

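### The microbiological outcome is described as incidence of MDR and C. difficile infection, but its numerators count isolates and detections, with no first-isolate or episode rule stated

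*Protocol article*

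**What the plan says.** **The claim.** The Abstract (Methods) lists, among the data that will show the platform's impact, "and the incidence of infections caused by multidrug-resistant bacteria and" *C. difficile*. The closing paragraph of the Discussion gives "reducing infections caused by MDR bacteria and" *C. difficile* as an expected benefit.

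**The measure.** Section 2.5 records the "number of isolations of MDR microorganisms", to be counted "in clinical samples and also in nasal and rectal or perineal swab samples (only in selected NHs"), and the "number of DNA or toxin detection for" *C. difficile* in clinical samples. Table 2 (section 2.4) fixes the platform indicators in the same terms. Numerators are monthly isolate counts for each organism, for example "Monthly number of methicillin-resistant" *S. aureus* isolates, plus "Monthly detection of DNA or toxin for" *C. difficile*. The denominator is "Number of residents in the month".

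**What is not stated.** The article gives no criterion that turns a positive result into an infection, and no rule for a second positive from the same resident. Table 3 (section 2.7.1) classifies resistance only.

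**The concern.** An isolate count is not an incidence of infection. Read literally, a resident with ESBL *E. coli* in one urine sample, in a repeat urine and in a wound swab contributes three to the numerator. A positive culture may reflect colonisation. A *C. difficile* DNA result without toxin counts the same as a toxin-positive one.

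This matters if the number of positives recorded per affected resident differs between phases. The documents describe two ways in which it could:

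- **Sampling.** Clinical samples are taken on clinical indication (section 2.6.1), so sampling depends on staff judgement. The intervention trains those staff in diagnosing and treating the main infectious syndromes (Discussion).
- **Counting.** Collection moves from an Excel form before the intervention to the platform during it (section 2.5), where participants enter the numerators (section 2.4). Clinical samples are analysed in each center's own laboratory (section 2.6.1). Without a stated rule, repeats may be handled differently between phases or centers.

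The segmented regression in section 2.9 estimates a level change at the interruption. It cannot tell a shift in recorded positives per case from a change in cases.

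**Working it through.** The plan gives no incidence, repeat rate, effect size or power for this outcome, so there is no figure of its own to reproduce.

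**1. Claim against measure.**

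| Element | Abstract and Discussion | Section 2.5 and Table 2 |
|---|---|---|
| MDR bacteria | infections | isolates |
| *C. difficile* | infections | DNA or toxin detections |
| Repeat positives | an incidence implies new cases | no rule stated |
| Colonisation, DNA-only results | not infections | not excluded |

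**2. Effect on the comparison.** Let *k* be the number of recorded positives per true case in a phase. Repeats raise *k*, and so do positives without infection. Then

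recorded rate = (cases / residents in the month) × *k*

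apparent ratio = true ratio × (*k* after / *k* before)

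Set the true ratio to 1, so that nothing happens to the number of cases. All values of *k* are assumptions.

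| *k* before | *k* after | Apparent ratio |
|---|---|---|
| 1.5 | 1.5 | 1.5 / 1.5 = 1.00 |
| 1.5 | 1.2 | 1.2 / 1.5 = 0.80 |
| 2.0 | 1.5 | 1.5 / 2.0 = 0.75 |
| 1.2 | 1.5 | 1.5 / 1.2 = 1.25 |

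The first row shows that a constant overcount leaves the relative comparison intact. On an absolute scale it would multiply a real level change by *k*, but it would not create one. The other rows show that a change in *k* passes straight into the estimate, in either direction.

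**3. Reach.** Section 2.3.2 sizes the study on total antimicrobial consumption, which it calls the main variable. Neither the 9 centers nor the 10 after the loss allowance (9 / 0.90 = 10) uses a microbiological count, so the sample size does not depend on this definition.

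**The case against.** The strongest reply is that this is a labelling issue. Section 2.5 and Table 2 call these counts microbiological variables and indicators, not infections. The Discussion sentence states an expectation, and the Discussion also lists *C. difficile* detection among outcomes common in earlier studies. A de-duplication window is a detail that an article may leave to its full protocol. Clinical indication also limits incidental carriage.

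Much of this stands, and it rules out several stronger readings that a reader might infer:

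- **That every repeat positive is kept.** The text does not say so. It gives no rule, and a fuller protocol may hold one.
- **That repeats can never be removed.** Section 2.5 draws the data retrospectively from records that include those of the microbiology units, and section 2.4 lets participants modify entered data. A re-count looks possible.
- **That the bias favours the intervention.** Training in diagnosis could reduce or increase sampling, and the documents give no data on either.
- **That an artefact near 20% rivals the effect the study is sized for.** That 20% belongs to antimicrobial consumption.
- **That carrier swabs inflate the after-phase count.** They sit under the same variable in section 2.5 and are taken only in the intervention phase (section 2.6.1). Their stated use in section 2.9 is correlation with wastewater and clinical findings, and nothing says that they enter the before-after count.

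The mismatch itself is not answered. The article states the outcome in one place and fixes its numerators in another, and the two do not measure the same thing. Clinical indication reduces colonisation and DNA-only positives but does not exclude them.

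**Conclusion.** The point holds as a mismatch between claim and measure on a secondary outcome. Isolates and DNA-or-toxin detections per residents in the month, with no stated infection, first-isolate or episode criterion, do not support a statement about incidence of, or reduction in, infections.

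The bias is conditional. It needs recorded positives per case to change between phases, through sampling or through counting practice. Under the assumed shifts the apparent ratio runs from 0.75 to 1.25 with no change in cases. These figures show what such shifts would do; they do not estimate what will happen, because the documents give no repeat rates. The main variable and the sample size are untouched. The definition should be settled before the two phases are compared.

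**What to change.** - **Numerators.** Define the Table 2 MDR numerators as residents with a first clinical isolate, one per resident, organism and phenotype within a fixed window. The word *clinical* also keeps carrier swabs out of this count; report those separately.
- **Both phases.** Apply the rule identically before and during the intervention, put it in the platform's data-entry help, and re-count baseline from the same microbiology records.
- ***C. difficile*.** Count the first positive per resident per window. Report toxin-positive separately from DNA-only where laboratories record it. The article does not show that every center's laboratory does, so the split should not be a condition of the analysis.
- **Name.** Call the outcome *residents with a new MDR isolate* or *residents with a new C. difficile detection*. Drop the infection wording in the Abstract and Discussion unless an infection criterion is applied.

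The cost is one definition, a modest re-count and smaller counts. Smaller counts need not mean less relative precision. As an illustration, assume Poisson cases of which 70%, 20% and 10% yield 1, 2 and 4 isolates. The mean is 0.7 + 0.4 + 0.4 = 1.5 isolates per case and the mean square is 0.7 + 0.8 + 1.6 = 3.1. For the same number of cases, the squared relative error of the isolate count is then 3.1 / 1.5² = 1.38 times that of the case count.
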